### Power

3.5.

Our sample size (*n* = 200) is based on statistical power calculations with the primary outcome of detecting group differences in PEth-assessed alcohol abstinence across 11 assessments during treatment and 4 assessments in follow-up. Our missing data techniques will recapture some power lost due to attrition, but we take a conservative approach to ensure adequate power by basing power calculations on a sample size reduced by 25% (*n* = 150). Our pilot study found an increase in abstinence of 43% in the CM group compared to 0% in the Control group. Using methods previously described [45], this effect would result in >99% power with *n* = 150 when comparing abstinence among groups in treatment (G*Power software). While this effect is promising, CM meta-analyses and large RCTs consistently demonstrate odds ratios (ORs) as effect sizes ranging from 1.7 to 4.5 for increasing substance use abstinence [23,46–51]. In addition, CBT4CBT, which all participants will receive, has an effect size on substance use ranging from *d* = 0.11–0.37. These are modest and consistent with CBT interventions that are commonly paired with CM in past trials where CM demonstrated superiority to CBT [47,49,52]. Based on our pilot study, we expect an effect size no smaller than OR = 1.7, which accounts for the underlying effect of CBT in both groups. In the treatment and follow-up period, at a sample size of *n* = 150, we will have at least 80% power to detect a modest effect size of OR = 1.34.

For the secondary aim of reducing the frequency of PEth-defined excessive drinking, our group has consistently found secondary improvements in the odds of substance-related harms to be OR = 1.80 or larger. Assuming a sample size of n = 150, we estimate at least 80% power to detect an OR = 1.80 for reduction in PEth-defined excessive drinking during treatment or the follow-up period.

For analyses of the ANA, our proposed sample size of n = 150 will provide at least 80% power to identify an OR = 1.44 when there are as many as 10 predictors being modeled. This OR corresponds to a small but clinically meaningful change predicted by demographics, our ANA variables, and in-treatment PEth-defined abstinence.

Power for our economic analysis is based on assumptions regarding maximum willingness-to-pay value [53,54]. Using varying estimates from previous relevant RCTs conducted over similar time frames, we estimate at least 80% power that the intervention is a good value at the recommended willingness-to-pay threshold of $150,000 per QALY [55].

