## Introduction

1.

Despite the availability of treatment options for alcohol use disorder (AUD), few individuals with AUD seek treatment [1]. Poor treatment utilization may result from barriers associated with in-person care, e.g., inconvenience, transportation costs, stigma [2]. During the COVID-19 pandemic, 60% of substance use disorder patients received some portion of their substance-related treatment via telehealth [3]. Prior to the pandemic, virtual treatments were also evaluated and disseminated as treatment options for patients with substance use disorders. These included online cognitive behavioral therapies, such as Computer Based Training for Cognitive Behavioral Therapy (CBT4CBT) and telehealth-based contingency management (CM) [4,5]. However, this work has focused on telehealth treatment for illicit drug use, while telehealth treatments for AUD are limited to pilot studies [6,7]. Telehealth interventions have potential limitations (e.g., access to and comfort with technology), however its advantages likely outweigh disadvantages for individuals with AUD who do not or cannot access in-person care. Randomized controlled studies evaluating the efficacy of telehealth-based treatment models for AUD are needed.

CM is ideal for telehealth delivery given its simple procedural nature, which consists of individuals receiving tangible reinforcers in exchange for meeting treatment goals (e.g., reducing substance use, maintaining abstinence). Initial telehealth and app-based CM models indicate reductions in drug and alcohol use (e.g., DynamiCare, FDA-approved reSET) [6–12,23,26,27]. For AUD, these telehealth-based CM models have utilized transdermal monitors or repeated daily breath sampling, which can be costly, burdensome, and stigmatizing for patients [6,7,9,11]. Another factor that can impact the efficacy of a telehealth-based CM model is the intervention duration. A meta-analysis found that CM was associated with a 22% higher odds of post-treatment illicit drug abstinence in comparison to other interventions, and that the best predictor of long-term abstinence was the length of the CM intervention [33]. The utilization of alcohol biomarkers that have a longer window of detection is one method to extend telehealth-based CM duration while also reducing burden on patients through decreased sampling and visit frequency.

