## Discussion

4.

This randomized controlled clinical trial assesses the efficacy of a telehealth-based CM intervention for AUD in a large national sample. Telehealth delivery has some potential limitations, such as access to and comfort with technology, but advantages, like reduced stigma and travel, likely outweigh the disadvantages. For instance, 64% of participants in our telehealth-based CM pilot study were treatment-naïve [7], suggesting that telehealth interventions might be a low-burden and low-barrier treatment option for individuals with AUD.

While CM is an evidence-based treatment for AUD and a powerful tool for initiating abstinence, evidence for sustained post-intervention effects is less conclusive [23,47,48,52,56]. In efforts to address this gap in CM research, the follow-up period for this study is 12 months in duration compared to 6 months in traditional CM models. Another strength of this study is the utilization of the ANA framework and alcohol biomarkers to identify potential predictors of treatment response and long-term outcomes. These predictors could provide opportunities to improve treatment efficacy and better direct care for this population (e.g., individualized treatment approaches). Lastly, this study will fill a critical gap in the CM literature by providing essential information for providers regarding resource and cost requirements for implementing this telehealth-based CM model.

A limitation of the study is that there is up to a one-week delay between submission of blood samples and provision of CM reinforcers. If we do not observe an effect of CM on outcomes, it could be a result of this delay. However, in our pilot study, CM participants did not report concerns regarding the week delay (i.e., surveys and qualitative interview) and achieved levels of alcohol abstinence consistent with previous CM studies [7]. Another potential limitation is the increased burden for the CM group, depending on how long participants remain in the Starting Phase. More visits might contribute to higher attrition in the CM condition, or it could lead to lower levels of attrition because individuals who are unable to achieve long-term abstinence (i.e., <20 ng/mL) will have more frequent visits and a lower bar for achieving reinforcers. The effects of an adaptive reinforcement schedule on attrition rates in the CM group will be assessed.

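### The power section gives treatment and follow-up one effect floor (OR 1.7) and one power claim (80% at OR 1.34); neither is supported for follow-up, where the article's only post-treatment figure is OR 1.22

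*Protocol article*

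**What the plan says.** The last paragraph of the Introduction puts both the intervention and the follow-up period inside the primary aim. Section 3.2 gives each its own logit GEE, with 11 assessments in treatment and 4 in follow-up.

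Section 3.5 (Power) then makes these statements:

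- The pilot: "Our pilot study found an increase in abstinence of 43% in the CM group compared to 0% in the Control group". This is used for a power figure above 99% "when comparing abstinence among groups in treatment (G*Power software").
- The literature: CM meta-analyses and large trials are said to show consistently "odds ratios (ORs) as effect sizes ranging from 1.7 to 4.5 for increasing substance use abstinence". The range is not labelled as in-treatment or post-treatment.
- The expectation: "Based on our pilot study, we expect an effect size no smaller than OR = 1.7, which accounts for the underlying effect of CBT". No period is named.
- The power claim, introduced as covering both treatment and follow-up at n = 150: "we will have at least 80% power to detect a modest effect size of OR = 1.34".

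Two passages elsewhere bear on the period after CM ends. The Introduction reports from a meta-analysis that "CM was associated with a 22% higher odds of post-treatment illicit drug abstinence in comparison to other interventions", and adds that "the best predictor of long-term abstinence was the length of the CM intervention". The Discussion says that "evidence for sustained post-intervention effects is less conclusive". Section 3.5 does not mention the 22% figure and gives no effect specific to follow-up.

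**The concern.** A CM effect while rewards are contingent on the biomarker and a CM effect up to a year after they end are different quantities. Section 3.5 covers both with one floor. It credits that floor to a pilot whose only comparison cited there is in treatment. The one post-treatment number in the article is smaller than the floor and smaller than the OR said to be detectable.

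Durability is the gap that the Discussion says the trial will help to fill. If the true follow-up effect is modest, a non-significant result would be reported from an analysis advertised as having at least 80% power. Readers could then take it as evidence that the CM effect wears off, when the analysis could not have told the two cases apart.

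**Working it through.** **Inputs from the article.** 200 randomized (2.1). Power based on 25% fewer, so 150 (3.5). Four follow-up assessments in a separate logit GEE (3.2). Alpha 0.05 (3.1). ORs of 1.7 and 1.34 (3.5) and 1.22 (Introduction). On the log scale these are ln 1.7 = 0.5306, ln 1.34 = 0.2927 and ln 1.22 = 0.1989.

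**Assumptions, not given in the article.** 1:1 allocation (75 per arm), two-sided test, exchangeable within-person correlation ρ from 0 to 0.5, and control abstinence rate scanned from 0.10 to 0.65 with the most favourable value used.

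**Step 1: the pilot figure reproduces.** For 43% versus 0% at 75 per arm, the null SE is √(2 × 0.215 × 0.785 / 75) = 0.0671 and the alternative SE is √(0.43 × 0.57 / 75) = 0.0572. Power = Φ((0.43 − 1.96 × 0.0671) / 0.0572) = Φ(5.22), above 99.9%.

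**Step 2: accept the 80% at OR 1.34 as printed.** The implied SE is 0.2927 / (1.960 + 0.842) = 0.1045.

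- Power at OR 1.22, n = 150: Φ(0.1989 / 0.1045 − 1.960) = Φ(−0.056), about 48%.
- With all 200 retained: Φ(1.903 × √(200/150) − 1.960) = Φ(0.238), about 59%.
- Sample needed for 80% at OR 1.22: (0.2927 / 0.1989)² = 2.17 times as large, so about 325 analysed, or 325 / 0.75 = about 433 randomized.

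This step needs no control rate or correlation.

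**Step 3: compute follow-up power directly.** Effective observations per arm = 75 × 4 / (1 + 3ρ). SE = √(V / effective n), with V = 1/[p₀(1 − p₀)] + 1/[p₁(1 − p₁)]. Power = Φ(ln OR / SE − 1.960).

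- OR 1.22, ρ = 0, control rate about 0.475: SE = 0.1635; Φ(0.1989 / 0.1635 − 1.960) = Φ(−0.744), 23%.
- OR 1.22, ρ = 0.5: effective n = 120, SE = 0.2585; Φ(−1.191), 12%.
- OR 1.34, ρ = 0, control rate about 0.46: V = 8.043, SE = √(8.043 / 300) = 0.1637; Φ(0.2927 / 0.1637 − 1.960) = Φ(−0.173), 43%.

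Best-case follow-up power, four visits:

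| OR | Analysed | ρ = 0 | ρ = 0.2 | ρ = 0.3 | ρ = 0.5 |
|---|---|---|---|---|---|
| 1.22 | 150 | 23% | 16% | 14% | 12% |
| 1.22 | 200 | 29% | 20% | 17% | 14% |
| 1.34 | 150 | 43% | 29% | 25% | 20% |
| 1.34 | 200 | 54% | 37% | 32% | 26% |
| 1.7 | 150 | 90% | 72% | 65% | 53% |

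**Step 4: could another reading recover 80% at OR 1.34 in follow-up?** It needs about 8.043 / 0.1045² ≈ 737 independent observations per arm, and 75 × 4 = 300 is the ceiling. A one-sided test gives Φ(1.787 − 1.645), about 56%. The figure can be reached if 1.34 is an OR per standard deviation of a continuous predictor. At an abstinence rate of 50%, (1.960 + 0.842)² / (0.25 × 0.2927²) = about 367 observations in total, against 600 / (1 + 3ρ), which allows ρ up to about 0.21. That is not the contrast between two arms.

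**The case against.** The strongest reply is that 1.22 is the wrong yardstick. It concerns illicit drugs rather than alcohol and pools CM against other interventions. The abstract says CM usually lasts 12–16 weeks, and the sentence that gives the 22% goes on to name CM duration as the best predictor of long-term abstinence. The authors extend CM to 26 weeks for that reason, and planning for a larger effect is a legitimate judgement. This stands, so 1.22 belongs in the plan as a pessimistic scenario, not as the expected effect. It does not rescue the floor, because the article puts no OR on the benefit of 26 weeks. Section 3.5 also borrows across substances itself when it cites 1.7 to 4.5 for substance use.

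Three stronger readings are tempting, and the article does not support them:

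- *Follow-up was sized on 1.7.* It was not. 1.7 is the stated expectation and 1.34 the stated detectable effect.
- *The 1.7–4.5 range is an in-treatment range carried into follow-up.* It is unlabelled. References 23, 47 and 48, cited for it, are cited again in the Discussion on sustained effects, so it may include post-treatment estimates. Only the pilot contrast is clearly in treatment.
- *The Discussion concedes a small post-treatment effect.* It describes inconclusive evidence and gives no size.

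One could also read the 1.34 claim as pooling all 15 assessments (75 × 15 = 1,125 per arm). That would reach 737 only for ρ up to (1,125/737 − 1)/14, about 0.04, and section 3.2 specifies separate models.

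**Conclusion.** The point holds for follow-up, on two counts. First, the expectation of at least OR 1.7 has no stated post-treatment support, and the article's only post-treatment figure is below both 1.7 and 1.34. On the plan's own terms, power at that figure is about 48%, or 59% with full retention. Second, the printed follow-up claim is not delivered by the design as described: at most 43% at OR 1.34 under a two-sided test, even with zero within-person correlation and the best control rate.

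The 48% and the 12–23% rest on different premises and should not be combined. The first accepts the printed claim; the second replaces it. The direct figures depend on 1:1 allocation, a two-sided test and exchangeable correlation. The shortfall at OR 1.34 holds for any non-negative correlation, and for a one-sided test too. A reader might infer that the follow-up analysis is bound to fail. That does not follow: at OR 1.7 best-case power is 53–90% for ρ from 0.5 to 0, and the true effect is unknown.

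**What to change.** In section 3.5:

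1. State expected effect and power separately for treatment and follow-up.
2. Limit the floor of 1.7 to treatment unless a post-treatment source for it is given.
3. Replace the follow-up power statement with one computed for four assessments, with the control abstinence rate, within-person correlation, allocation ratio and sidedness stated. Show it over a range of ORs that includes 1.22 as a pessimistic scenario.
4. Do not print the new figures beside an unrevised 80% at OR 1.34, because the two cannot both be true.
5. Add one sentence saying that a non-significant follow-up contrast will be interpreted through its estimate and 95% confidence interval.

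The cost is a short recalculation and a few sentences. Sample size, visits and procedures do not change. The downside is that the stated follow-up power becomes clearly less favourable.

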### Preliminary analyses

3.1.

Our data and supporting documents will be submitted to the National Institute on Alcohol Abuse and Alcoholism’s National Data Archive (NDA) and will be available within three years of completion of the study. Groups will be compared for differences in demographics and pre-treatment alcohol use. Means and standard deviations will characterize continuous variables, and percentages and frequencies characterize categorical variables. We will assess the impact of sex as a biological variable. Our alpha threshold for statistical significance will be 0.05.

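### The stated 80% power at OR = 1.34 cannot hold for the follow-up group comparison, and in treatment it needs nearly independent repeated samples

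*Protocol article*

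**What the plan says.** Section 3.5 bases the sample size on the "primary outcome of detecting group differences in PEth-assessed alcohol abstinence", assessed "across 11 assessments during treatment and 4 assessments in follow-up". Power is computed for 150 participants, which is 200 less 25% for attrition. The section says that "we expect an effect size no smaller than OR = 1.7". Then, for treatment and follow-up at n = 150, it says that "we will have at least 80% power to detect a modest effect size of OR = 1.34". For the secondary outcome, on the same n, it says that "we estimate at least 80% power to detect an OR = 1.80 for reduction in PEth-defined excessive drinking during treatment or the follow-up period".

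Section 3.2 (Treatment efficacy) fits separate logit GEE models to the two periods, so each period has to reach its stated power on its own data. Section 3.1 says: "Our alpha threshold for statistical significance will be 0.05". The article gives no within-person correlation, Control abstinence rate or sidedness for the OR = 1.34 figure. For the pilot-effect calculation it refers to a cited method and to G*Power.

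**The concern.** Group is a between-person factor. Repeated PEth results from one person add less information about a group difference than the same number of results from different people, and the discount grows with within-person correlation. Treatment has 11 assessments and follow-up has 4, so follow-up has little more than a third of the samples. One detectable OR for both periods therefore looks wrong on its face, and 1.34 is small for 150 people.

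The figure matters because it is the plan's safety margin. The expected effect is an OR of at least 1.7, and a detectable OR of 1.34 tells the reader there is room to spare. The Discussion presents the 12-month follow-up as a main contribution. If the detectable effect there is overstated, a null follow-up result could be given more weight than the data can bear.

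**Working it through.** **Inputs from the article.** Alpha is 0.05; n = 150; m = 11 assessments in treatment and 4 in follow-up; the models are separate for each period.

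**Assumed, because not stated.** Allocation is 1:1 (75 per arm, the most favourable split) and the test is two-sided. The Control rate p0 is scanned for its best value. The correlation ρ is exchangeable and starts at 0.

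**Formulas.** Effective n per arm = 75m / (1 + (m − 1)ρ). With p1 the rate implied by the OR, SE(ln OR) = √[1/(n·p0·(1 − p0)) + 1/(n·p1·(1 − p1))]. Power = Φ(ln OR / SE − 1.96). ln 1.34 = 0.2927.

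**The plan's own figures first.** The pilot statement (43% against 0%, 75 per arm, power above 99%) reproduces. For OR 1.34 in treatment at ρ = 0, n = 75 × 11 = 825 per arm:
- p0 = 0.30: p1 = 0.365, SE = 0.1049, power = Φ(2.790 − 1.96) = 79.7%, detectable OR 1.34.
- p0 = 0.465 (the best case): p1 = 0.538, SE = 0.0987, power = Φ(2.964 − 1.96) = 84%.

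So the stated figure can be obtained for treatment, with independent samples.

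**How much correlation treatment tolerates.** At p0 = 0.465, 80% power needs n = (1.96 + 0.842)² × (4.020 + 4.023) / 0.2927² ≈ 737 independent samples per arm. Setting 825 / (1 + 10ρ) = 737 gives ρ ≈ 0.012. With AR(1) correlation the limit is a lag-1 value of about 0.06. Even full independence is not enough if p0 is below about 30% or above about 63%.

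**Follow-up.** At ρ = 0, n = 75 × 4 = 300 per arm, against 737 needed. At p0 = 0.465, SE = 0.1637 and power = Φ(1.787 − 1.96) = 43%. The detectable OR is about 1.59 at best.
- One-sided: Φ(1.787 − 1.645) = 56%.
- All 200 participants, 400 per arm: SE = 0.1637 × √(300/400) = 0.1418, power = Φ(2.064 − 1.96) = 54%.
- Correlation needed for 80%: (300/737 − 1)/3 ≈ −0.20, which is not plausible for one person's repeated PEth results.

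**Illustration with assumed correlations (p0 from 20% to 50%, n = 150).**

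| ρ (assumed) | Detectable OR, treatment | Detectable OR, follow-up | Best-case power at OR 1.34, treatment / follow-up |
|---|---|---|---|
| 0.1 | 1.48–1.59 | 1.69–1.84 | 55% / 35% |
| 0.3 | 1.75–1.90 | 1.89–2.07 | 32% / 25% |
| 0.5 | 1.99–2.18 | 2.09–2.30 | 23% / 20% |

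At ρ = 0.1 and an OR of 1.7, the same formula gives power of 90–97% in treatment and 68–81% in follow-up.

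**OR = 1.80 for excessive drinking, follow-up.** With a 20% rate in the arm with less excessive drinking (31% in the other), 80% power needs about 248 independent samples per arm, so ρ can be at most (300/248 − 1)/3 ≈ 0.07. With 40% (against 55%) it needs about 186, so ρ can be at most about 0.20. The claim can hold, but only within such limits.

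**The case against.** The strongest reply is that this is a condensed article. The calculation may rest on a cited method and software settings that are not printed, and leaving out a correlation or Control rate is no error in itself. That is right as far as it goes, and it limits what can be said about treatment. There, 1.34 is attainable at near-zero correlation. A reader might infer that the authors treated 1,650 samples as independent, but the match at a 30% Control rate is a back-fit and does not show what they did. It does not rescue follow-up, because no non-negative correlation, Control rate or choice of sidedness brings 600 samples to 80% power for this effect.

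Other readings could produce the number but do not fit the text:
- **Group-by-time interaction.** With OR 1.34 converted to f = 0.081, a repeated-measures interaction test in follow-up has 87% power at ρ = 0.7 (64% at 0.5). The interaction is in the model, but section 3.5 says it is powering group differences.
- **OR per standard deviation of a continuous predictor.** The section sets 1.34 beside group ORs of 1.7 to 4.5, so it is a group contrast.
- **Pooling all 15 visits.** This still needs ρ of about 0.04 or less, and section 3.2 fits separate models.

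It is also fair to say that correlations of 0.1 to 0.5 appear nowhere in the article. During the Starting Phase the outcome is a week-over-week decrease. Successive decreases share a measurement and may even be negatively correlated. The table is therefore an illustration, not a finding about this trial.

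Two stronger readings are tempting and not supported. One is that the OR = 1.80 claim implies a different correlation from the OR = 1.34 claim. It does not: any correlation that gives 80% power at 1.34 gives more at 1.80 for a like outcome, the claim is only of at least 80%, and the outcome is a different one. The other is that the Introduction, where "CM was associated with a 22% higher odds of post-treatment illicit drug abstinence in comparison to other interventions", contradicts the planning effect of 1.7. That result concerns illicit drugs. The same sentence names intervention length as the best predictor of lasting abstinence, which supports the longer programme tested here, and 1.7 is argued from the pilot and other CM trials.

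**Conclusion.** The power statement is wrong as written for follow-up. At OR 1.34, power for the between-group effect is at most 43% against the claimed 80%, and the detectable OR is at best about 1.59. This rests only on 75 per arm, 4 assessments, two-sided 0.05 and non-negative correlation.

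For treatment the statement is not proven wrong, but it needs a correlation of at most about 0.012 and a Control rate of about 30% to 63%. That is hard to believe across the whole period. The Introduction says PEth is detectable for up to 28 days, and Control samples are taken at intervals of one to four weeks (section 2.3.3).

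A reader might go on to infer that the trial is underpowered for its own expected OR of 1.7. The documents do not settle that. At an assumed correlation of 0.1, treatment power at 1.7 is ample and follow-up power is borderline; at 0.3 and above the detectable OR exceeds 1.7 in both periods. What can be said is that the margin implied by 1.34 is not assured, least of all in follow-up.

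**What to change.** Replace the single OR = 1.34 sentence in section 3.5 with two detectable ORs, one for treatment and one for follow-up. Each should come with the Control abstinence rate, within-person correlation and sidedness used, preferably over a small range of correlations. The inputs should be the authors' own, and the ranges above only show the scale to expect. If 1.34 was meant for another effect, such as the group-by-time interaction, the text should say so and give the group-difference figure beside it.

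State the event rate and correlation behind the OR = 1.80 follow-up claim in the same way.

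The cost is a short recalculation and a few sentences. Sample size, design and analysis do not change, and the stated sensitivity will look less favourable.
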